### Randomization

Randomization of program rollout timing was based on a simple random-number draw in Stata. The number of treated areas in phases 1 and 2 was determined based on logistical feasibility and an initial agreement between the municipality and the project team: in phase 1, nine areas were chosen for home visits and two for center-based programs. In phases 2 and 3, program reach was gradually increased to reach all communities as outlined in the “Study design” section above. In phase 1, 11 neighborhoods will receive the intervention; in phase 2, 27; in phase 3, all B and C neighborhoods will receive the interventions. Figure 3 summarizes the neighborhood selection process and shows the random allocation of interventions by phase. Figure 4 shows the spatial location of areas chosen for each intervention phase.

**Fig. 3 Fig3:**
[figure not shown]
Neighborhood selection and randomization

**Fig. 4 Fig4:**
[figure not shown]
Spatial distribution of program rollout phases. Notes: all A areas (green) are scheduled to be reached in a later stage (year 4) of the program

### Recruitment

Recruitment for this project will be implemented in close collaboration with the Municipality Secretariat for Social Wellbeing and Health (SSWH). The SSWH identifies eligible pregnant women each month, and links them to the project team. Each woman is then visited by study staff and, conditional on their consent, completes a baseline interview. According to the municipality of Boa Vista, there are approximately 600 new pregnancies per month. The baseline forms are then used to establish eligibility for the program. As stated above, the following three (non-mutually exclusive) groups of women are eligible for the program:
Household classified as poorPregnant women under age 20 years (teenage pregnancies)Women with previous exposure to partner violence

In the first few years of the program, a small sample of women with children under age 1 year will also be enrolled. This sample will be used to assess the relative impact of reduced exposure to the interventions.

In order to achieve enrollment to reach the sample size, the research group hired and trained a team of interviewers that will visit the eligible participants from the municipality list, but also actively search for other potential participants in the field. The research team will use the municipality official birth records on a monthly basis to monitor any unenrolled new children born in the catchment areas and enroll them afterwards.

Given that we will have 12,000 participating households in the intervention, we do not foresee any difficulties reaching the 3000 sample-size target for the endline.

#### Blinding

Given the nature of the intervention, blinding of participants is not possible. Endline interviewers will be blind to group assignment.

### Monitoring and potential harm

Given that the intervention does not present a risk for the population and that the municipality has committed to delivering interventions following the established timeline, there are no formal stopping rules for this trial. We also do not foresee needing any interim analysis for such purposes. However, even if not related to the intervention, the home visitor or group facilitator reports, or is informed of, any adverse event such as domestic violence, or health risk, which will be reported to the supervisor and to the Social Service Unit manager and relevant regulatory bodies as required, indicating expectedness, seriousness, severity, and causality.

### Sample size and power calculations

Based on the estimated number of births in the targeted B and C areas, we anticipate completing approximately 12,000 baselines (screening interviews) over the project period. Out of these mother-child dyads, we will randomly select 3000 for the endline assessment. We assume an average causal effect of 0.5 standard deviations (SD) for compliant mothers. With an anticipated average compliance rate of 50%, the study is powered to detect an intention-to-treat effect of 0.25 SD with power 0.9 between each of the two intervention arms and the control arm, assuming an average sample of 120 households in each of the 11 neighborhoods treated in phase 1, and an average sample of 60 households in each of the 28 control neighborhoods, assuming an intra-class correlation of 0.02.

In order to assess spillovers within households, we will also assess all older siblings under age 4 years in households selected for endline. Based on the high fertility rates observed at baseline, we anticipate a sample of 750 older siblings. Assuming a uniform distribution of siblings across clusters, the study is powered to detect a 0.3-SD change in PRIDI score with power 0.8.

In order to assess domain-specific changes in children’s development, we will also invite 80 mothers from each arm for a detailed assessment using Bayley’s Scales for Infant and Toddler Development (BSID-III). For these assessments, we will randomly select mothers from the control group as well as compliant mothers from the two intervention arms.

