### Trial design

The study was designed as a stepped-wedge, cluster randomized controlled trial with three arms. Arm 1 represents intervention delivered through fortnightly home visits; Arm 2 consists of the same content delivered through fortnightly center-based group meetings; Arm 3 is the control group.

To avoid contamination, neighborhoods were used as units of randomization. All 53 neighborhoods in Boa Vista were classified according to the municipality vulnerability criteria. Only neighborhoods classified as B (medium vulnerability) and C (high vulnerability) will be targeted by the program. As of 2017, 42 neighborhoods were in this category.

Three neighborhoods had either existing home-visiting programs or other planned interventions, and were excluded from the study, leaving a final study sample of 39 neighborhoods. Figure 2 presents the neighborhoods vulnerability distribution.

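### The endline sampling rule and the sibling power imply about 77 households per neighborhood, while the primary power assumes 120 and 60; the layout should be fixed and used throughout, though the effect on power is modest

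*Protocol article*

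**What the plan says.** All of this stands in the protocol article, mainly under Sample size and power calculations.

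- **Pool:** "we anticipate completing approximately 12,000 baselines (screening interviews) over the project period".
- **Endline rule:** "Out of these mother-child dyads, we will randomly select 3000 for the endline assessment". No stratum, quota or sampling fraction by area or arm is given.
- **Primary power:** the study is said to be "powered to detect an intention-to-treat effect of 0.25 SD with power 0.9 between each of the two intervention arms and the control arm". This claim rests on a layout of unequal numbers per area. For the treated side the section gives it as "assuming an average sample of 120 households in each of the 11 neighborhoods treated in phase 1"; the 28 control areas are put at 60 households each, on average. The ICC used is 0.02.
- **Siblings:** all older siblings under 4 in the endline households are to be assessed, 750 in expectation. "Assuming a uniform distribution of siblings across clusters", power is put at 0.8 for 0.3 SD.

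Two other sections matter. Trial design excludes three areas, "leaving a final study sample of 39 neighborhoods". Randomization describes a simple random-number draw and says that "in phase 1, nine areas were chosen for home visits and two for center-based programs".

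**The concern.** The section describes the endline sample in ways that do not fit together. A single random draw treats every dyad alike, so it gives phase-1 areas 120 households on average, and control areas 60, only if phase-1 areas have twice as many baselines each. Nothing in the article suggests this, and random allocation gives no reason to expect it. The sibling calculation then uses an even spread across clusters, although those siblings live in the households to which the primary calculation gives a 2:1 spread per area.

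The stake is where the assessments fall. Run as a simple random draw, endline would be expected to move several hundred assessments from the treated areas, where clusters are few, to the control areas. In the center-based arm, the sizes of two neighborhoods would alone decide how many children are assessed.

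**Working it through.** **Inputs from the article.** 12,000 baselines; 3000 endline households; 39 areas, of which 9 home-visit and 2 center-based in phase 1, with 28 controls; 120 and 60 households per area; ICC 0.02; effect 0.25 SD; 750 siblings, effect 0.3 SD.

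**Assumptions.** Two-sided 5% test (alpha is not stated in the section), normal approximation, SD 1, and ICC 0.02 for siblings too (none is stated for them).

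**Step 1: the two layouts.**
- Power layout: 11 × 120 + 28 × 60 = 1320 + 1680 = 3000, so it matches the stated total.
- One sampling fraction: 3000/12,000 = 25%, and 3000/39 = 76.9 per area if areas are similar in size. Phase-1 areas then give 11 × 76.9 = 846 households rather than 1320 (home 692 rather than 1080, center 154 rather than 240), and controls give 2154 rather than 1680.
- For a 25% draw to give 120 and 60, phase-1 areas would need 120/0.25 = 480 baselines each and controls 60/0.25 = 240. The 11 areas, 11/39 = 28% of clusters, would hold 1320/3000 = 44% of the pool.

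**Step 2: siblings.** The rate is 750/3000 = 0.25 per endline household. A uniform spread gives 750/39 = 19.2 per area, which is 0.25 × 76.9. The 120/60 layout gives 30 and 15 per area (11 × 30 + 28 × 15 = 750). The sibling assumption therefore fits the equal spread, not the layout used for the primary power.

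**Step 3: primary power.** With k clusters of m households, each arm contributes variance [1 + (m − 1) × 0.02]/(k × m). SE is the root of the two arms' sum, and power is Φ(0.25/SE − 1.96).

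| Comparison | Layout | Variance | SE | Power |
|---|---|---|---|---|
| Home, 9 v 28 | 120/60 | 3.38/1080 + 2.18/1680 | 0.0665 | 0.96 |
| Home, 9 v 28 | 77/77 | 2.52/692 + 2.52/2154 | 0.0693 | 0.95 |
| Center, 2 v 28 | 120/60 | 3.38/240 + 2.18/1680 | 0.1240 | 0.52 |
| Center, 2 v 28 | 77/77 | 2.52/154 + 2.52/2154 | 0.1324 | 0.47 |

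The stated 0.9 for each arm is not reproduced on the article's own inputs: the home arm is above it and the center arm far below it. A one-sided 5% test lifts the center arm at 120/60 only to 0.64. It passes 0.9 (0.95) only if the ICC is set to zero.

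**Step 4: sibling power, home versus control, 0.3 SD.**
- Uniform (19.2 per area): 1.365/173 + 1.365/538, SE 0.102, power 0.84.
- 30/15: 1.58/270 + 1.28/420, SE 0.094, power 0.89.

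**Step 5: unequal neighborhood sizes.** The article gives no sizes, so this step is illustrative. I simulated gamma-distributed sizes with an assumed coefficient of variation (CV) of 0.5 to 1.0 and a multinomial draw of 3000 (4000 replicates). Mean home-arm power is 0.94 to 0.89 with a mixed model and 0.92 to 0.83 with unweighted regression. Center-arm power is 0.45 to 0.39 with a mixed model.

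**The case against.** The best defense is that random selection does not exclude stratification. The power layout sums exactly to 3000, which suggests that one plan lies behind both sentences, and a journal article may leave sampling strata to the full protocol. A uniform distribution of siblings could also mean a constant 0.25 siblings per household, which would give 30 and 15 per area and agree with 120/60.

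Much of this stands. The sampling rule and the 120/60 layout can be reconciled by a stratified draw, so a reader who infers a proven contradiction between them goes too far. The sibling sentence, however, speaks of a spread across clusters, and read plainly that is the even spread. If the draw is stratified, the sibling sentence needs rewording; if it is not, the primary layout does.

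Four stronger readings are not supported:

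- **Three incompatible samples.** There are two, since 19.2 siblings per area is 0.25 × 76.9.
- **A certain loss of 36% of the treated sample** (846 against 1320). The 77 per area is an expectation under similar neighborhood sizes; actual sizes are not given.
- **Home-arm power falling below 0.9.** With equal sizes it is 0.95. A fall below 0.9 needs an assumed spread of sizes at the upper end of the range in Step 5, or a middling spread with an unweighted analysis.
- **The sampling rule as the cause of the center arm's low power.** It is about 0.5 under either layout, because that arm has two clusters.

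**Conclusion.** The point holds as an inconsistency of modest size. On the wording given, the endline rule and the sibling assumption point to an even spread of about 77 households and 19 siblings per area, while the primary power uses 120 and 60. The choice of layout moves home-arm power by about one point and center-arm power by about five. It leaves sibling power for home versus control above the stated 0.8 either way, and the uniform assumption is the more cautious of the two. These figures rest on a two-sided 5% test, a normal approximation, ICC 0.02 and equal sizes within each group of areas. Unequal sizes would cost more under a proportional draw, by an amount that the article does not allow one to fix.

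The claim of 0.9 for each arm fails in the center-based arm under both layouts. That shortfall is larger than anything the sampling rule causes.

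**What to change.** State that the endline draw is random within neighborhood, with targets of 120 dyads in each phase-1 area (or all available if fewer) and 60 in each other area. Compute the sibling power on the same spread, about 30 and 15 per area, and drop the uniform assumption.

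If a simple random draw is kept, restate the layout as about 77 per area and give the power for it, allowing for unequal neighborhood sizes.

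In either case, report power separately for 9 versus 28 and 2 versus 28 clusters and withdraw the single figure for each arm. Quotas hold the treated sample at its planned size where enough dyads exist, but they leave the center arm near 0.5.

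The cost is a sentence on sampling and a few recomputed figures, with no extra participants. It should be settled before endline opens, scheduled for April 2020 in the Timeline section. One small downside is that sampling fractions will differ by neighborhood, so municipality-wide descriptive figures need weights.

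### The stated power of 0.9 for each intervention arm cannot be reproduced for the center-based arm, which has two phase-1 neighborhoods and about 0.5 power at the plan's own inputs

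*Protocol article*

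**What the plan says.** Under Sample size and power calculations, the protocol article claims the trial is "powered to detect an intention-to-treat effect of 0.25 SD with power 0.9 between each of the two intervention arms and the control arm". The 0.25 SD is an effect of 0.5 SD in compliant mothers multiplied by 50% compliance. The inputs follow in the same sentence: "assuming an average sample of 120 households in each of the 11 neighborhoods treated in phase 1", "an average sample of 60 households in each of the 28 control neighborhoods", and "assuming an intra-class correlation of 0.02". No significance level or sidedness is given.

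The split of the 11 treated areas appears under Randomization: "in phase 1, nine areas were chosen for home visits and two for center-based programs". The Methods paragraph of the Abstract gives the same nine and two, and the Timeline section confirms that two center-based areas were launched in phase 1. The 28 control areas are the 39 study neighborhoods less these 11, so areas that join in phase 2 count as control in the power calculation.

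**The concern.** The claim is made for each arm separately, but the treated clusters are entered only as a total of 11. In a cluster-randomized comparison the number of clusters in the smaller arm largely determines precision, and here that number is two. A figure that is right for nine areas, or for 11, need not be right for two.

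Testing both platforms is a stated aim, the Abstract names their relative cost-effectiveness, and the Background gives the lower cost of center groups as a reason for including them. If the center comparison has about an even chance of missing the planned effect while the protocol says one in ten, a null center result may be read as evidence that the cheaper platform does not work.

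**Working it through.** **Inputs.** From Sample size and power calculations: effect 0.25 SD, 120 households per treated area, 28 control areas of 60, ICC 0.02. From Randomization: nine home areas and two center areas. Assumed: two-sided alpha 0.05. The inputs match the planned endline total: 11 × 120 + 28 × 60 = 1320 + 1680 = 3000.

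**Formula.** On a scale with SD 1, for k areas of m households per arm:

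- design effect = 1 + (m − 1) × ICC
- variance of the difference = DE₁/(k₁m₁) + DE₀/(k₀m₀)
- power ≈ Φ(0.25/SE − 1.96)
- detectable effect at 90% power = (1.96 + 1.2816) × SE

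Design effects: treated 1 + 119 × 0.02 = 3.38; control 1 + 59 × 0.02 = 2.18. Control term: 2.18/1680 = 0.00130.

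**Trying to reproduce 0.9, then by arm.**

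| Comparison | Variance | SE | Power, normal | Power, t (df) | Detectable effect, 90% |
|---|---|---|---|---|---|
| All 11 treated vs 28 | 3.38/1320 + 0.00130 = 0.00386 | 0.062 | 0.98 | 0.97 (37) | 0.20 SD |
| Home, 9 vs 28 | 3.38/1080 + 0.00130 = 0.00443 | 0.067 | 0.96 | 0.95 (35) | 0.22 SD |
| Center, 2 vs 28 | 3.38/240 + 0.00130 = 0.01538 | 0.124 | 0.52 | 0.49 (28) | 0.40 SD |

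For the center arm, 0.25/0.124 = 2.016 and Φ(2.016 − 1.96) = 0.52.

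Home versus center: 3.38/1080 + 3.38/240 = 0.01721, SE 0.131, detectable effect 3.2415 × 0.131 = 0.43 SD.

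**Can another reading rescue 0.9 for the center arm?**

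- *One-sided alpha 0.05:* 0.64 (0.63 with t).
- *Unlimited households in the two center areas:* variance 0.02/2 + 0.00130 = 0.01130, SE 0.106, power 0.65. Unlimited households in the control areas as well: 0.02/2 + 0.02/28 = 0.01071, SE 0.104, power 0.68.
- *Smaller ICC:* 0.01 gives 0.70 and 0.005 gives 0.83. Power of 0.9 needs an ICC of about 0.002, a tenth of the plan's value.
- *More areas of 120 in the arm:* six against 28 gives 0.90; an even split of the 11 (5.5 against 28) gives 0.88.

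**Phase-2 center areas.** The Timeline section runs endline from April 2020 to July 2021 at age 2, so the children were born from about April 2018 to July 2019. Phase 2 began in July 2019. Its eight center areas therefore supply almost no endline children exposed from pregnancy. If endline were extended and all ten center areas were compared with the ten areas then still untreated, at 3000/39 ≈ 77 households each: DE = 1 + 76 × 0.02 = 2.52, variance 2 × 2.52/770 = 0.00655, SE 0.081, power 0.87 (0.83 with t on 18 df).

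**The case against.** The best defence is that the 120 is an average, alpha is unstated, and covariate adjustment may be planned elsewhere. The first two are answered above: neither unlimited households nor a one-sided test reaches 0.9. On the third, if adjustment removed half of both the between-area and within-area variance, a generous assumption, the SE would fall to 0.124 × √0.5 = 0.088 and power would be about 0.81, still short. Nor is this a detail that an article may leave to a fuller document: the figure and its inputs are printed.

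Some stronger readings a reader might infer do not stand:

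- *The authors pooled the 11 areas.* Pooling gives 0.98, not 0.9. An even split comes closer, at 0.88. The protocol does not show how 0.9 was obtained, so only the failure to reproduce it for the center arm is established.
- *The whole trial is underpowered.* The home-visit comparison exceeds 0.9.
- *A null center result will be misread.* It may be; a reported interval would show the imprecision.
- *A confirmatory test fails.* The protocol names a primary outcome and an intention-to-treat comparison across three arms, but sets no confirmatory order among contrasts.

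**Conclusion.** The power statement is wrong as written for one of the two arms it covers. At the plan's inputs, the center-based arm has power of about 0.5 for 0.25 SD, roughly 40 points below the claim, and would need an effect of about 0.40 SD for 90% power. The claim holds for home visits.

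The only added assumption is two-sided alpha 0.05, and the conclusion survives one-sided 0.05. The value of 0.5 is more likely generous than harsh. Small-sample methods suited to two treated clusters give less (a permutation test on area means gives about 0.4), though the protocol specifies only standard regression models, so the conclusion does not rest on them. The center areas also opened only in July 2018, so births there at the start of the April 2018 to July 2019 window precede the program.

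**What to change.** Replace the power sentence with arm-specific figures and state the alpha and sidedness used. At two-sided 0.05:

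- home versus control: about 0.96
- center versus control: about 0.5, detectable effect at 90% power about 0.40 SD
- home versus center: detectable effect at 90% power about 0.43 SD

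Add that a null center-arm result may reflect low precision, and report the center comparisons with confidence intervals. Naming a single confirmatory contrast is optional, a design choice rather than a correction.

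The cost is wording in the protocol and registry, and a less favourable stated power for the center arm. No households are added.

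Bringing in the eight phase-2 center areas should not be offered as a wording change. It would need endline extended beyond July 2021, would cut the control areas from 28 to 10, and would still give only about 0.87 (0.83 with t). Either leave it out or state those costs.

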### Outcomes

The primary study outcome is child development at age 2 years as assessed by the PRIDI Scale. The secondary study outcome is child survival, which will be assessed using data from the municipality’s vital registration system (SIM and SINASC). Maternal depression will be assessed using the Center for Epidemiologic Studies Depression Scale (CES-D Scale).

Intention-to-treat analysis will be used to compare outcomes across the three study arms.

Additional per-protocol analysis will be conducted using data on program compliance. Our primary measure of compliance in the home-visiting arm will be the number of home visits completed. Our primary compliance measure in the center-based groups will be the number of sessions attended by the mother. Table 1 presents the data collection overview.

**Table 1 Tab1:** Data collection overview

Data collection phase	Instruments
Baseline (12,000)	Participant identification, anthropometrics, and habits Socioeconomic characteristics Household characterisits Previous gestational information Maternal depression (EPDS) Neighborhood characteristics and social support Couples’ conflict Parental knowledge Maternal cognitive development (WAIS) Paternal characteristics
Main endline (*N* = 3000)	Child development (PRIDI) – Primary outcome Maternal depression (CES-D) Caregiver self efficacy (PSOC) Parental style (ACT) Parental knowledge Child anthropometrics (height and weight)
In-depth endline assessment (*N* = 240)	Attachment and caregiver interactions (OMCI) Bayley Scales for Infant and Toddler Development (BSID-III)
Qualitative interviews	Focus groups with child development agents and group-meeting facilitators Individual interviews with program beneficiaries divided by full compliers, non-compliers, and dropouts by intervention study arm

*ACT*, *BSID-III* Bayley’s Scales for Infant and Toddler Development, *CES-D* Center for Epidemiologic Studies Depression Scale, *EPDS* Edinburgh Postnatal Depression Scale, *OMCI* Observation of Mother-child interaction, *PRIDI* Regional Project on Child Development Indicators, *PSOC* Parenting Sense of Competence Scale, *WAIS* Weschsler Adult Intelligence Scale

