### Timeline

Baseline survey collection started on 1 December 2017 and will be finished by July 2020. The home-visits team was trained in November 2017 and visits were launched shortly after initiation of baseline in the phase-1 home-visiting areas; the first births within this group occurred in February 2018. Due to logistical challenges, center-based programs were started later; the two areas randomly selected for phase 1 of the project were formally launched in July 2018. Phase 2 (both for home visits and center-based programs) was started in July 2019, with 10 neighborhoods added to the home-visiting programs, and eight added to the center-based programs.

Endline surveys are scheduled to start in April 2020 and will target children at age 2 years. With the targeted sample size of 3000 households we anticipate to complete endline by July 2021. BSID-III assessments will start in July 2020 and should be completed within 6 months.

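### The BSID-III/OMCI sub-study takes only compliant mothers from the intervention arms but all-comers from the control arm, so its treatment contrasts are not protected by randomization

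*Protocol article*

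**What the plan says.** The section on sample size and power sets up a sub-study with the stated purpose "In order to assess domain-specific changes in children" and their development: "we will also invite 80 mothers from each arm for a detailed assessment" with the BSID-III. The sampling rule follows directly: "we will randomly select mothers from the control group as well as compliant mothers from the two intervention arms".

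Table 1, under Outcomes, lists the same component as "In-depth endline assessment (*N* = 240") and places the observation of mother-child interaction (OMCI) in it beside the BSID-III. The Timeline states that "BSID-III assessments will start in July 2020 and should be completed within 6 months".

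The Outcomes section measures compliance by the number of home visits completed in one arm and the number of sessions the mother attended in the other. It names intention-to-treat as the way to compare the three arms and adds a per-protocol analysis using compliance data. The Statistical methods section repeats both.

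On size, the article writes "We assume an average causal effect of 0.5 standard deviations (SD) for compliant mothers" and puts average compliance at 50%, so that "the study is powered to detect an intention-to-treat effect of 0.25 SD with power 0.9". That power statement concerns the main endline. None is given for the 240.

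**The concern.** A mother's compliance is her own behavior after assignment. Mothers who keep up fortnightly contact may differ from those who do not in stability, motivation, cognition or mental health, and these could predict a child's development with no program at all. The rule applies this filter to the intervention arms only. Control mothers who would have dropped out remain in their sample, because nobody can observe which ones they are.

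It makes no difference whether the compliers are drawn at random or all taken: non-compliers are absent from two arms and present in the third. The home-versus-center contrast is exposed as well, since being compliant means accepting visits in one arm and traveling to a center in the other.

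At stake is what the sub-study can conclude. A difference in BSID-III or OMCI scores could come from the program, from who was selected, or from both, and the 240 assessments cannot separate these. With no BSID-III data on intervention non-compliers, they support neither the intention-to-treat comparison named in the Outcomes section nor a standard instrumental-variable estimate of the effect in compliers.

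**Working it through.** **Inputs from the article:** 80 mothers per arm in three arms; compliance c = 0.5; complier effect 0.5 SD; intra-class correlation 0.02; 28 control neighborhoods and, in phase 1, two center neighborhoods.

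**Assumptions, not in the article:** two-sided 5% test; unit SD; normal approximation; g, the complier minus non-complier difference in untreated score, ranging from 0 to 0.6 SD.

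**1. The article's own figures.** 3 × 80 = 240, which matches Table 1. 0.5 × 0.5 SD = 0.25 SD, which matches the stated intention-to-treat effect.

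**2. The bias.** A random control sample mixes would-be compliers (share c) and non-compliers (share 1 − c). Its mean therefore lies (1 − c) × g away from the untreated mean of compliers, and

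expected contrast = complier effect + (1 − c) × g = complier effect + 0.5g.

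**3. Rejection of a true null.** SE = √(2/80) = 0.158. The rejection probability is P(Z > 1.96 − bias/SE) + P(Z < −1.96 − bias/SE).

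| g (SD) | Bias (SD) | Rejection if true effect is 0 | Expected contrast if true complier effect is 0.5 SD |
|---|---|---|---|
| 0 | 0 | 5% | 0.50 |
| 0.1 | 0.05 | 6% | 0.55 |
| 0.2 | 0.10 | 10% | 0.60 |
| 0.3 | 0.15 | 16% | 0.65 |
| 0.4 | 0.20 | 24% | 0.70 |
| 0.5 | 0.25 | 35% | 0.75 |
| 0.6 | 0.30 | 48% | 0.80 |

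At g = 0.5 the bias equals the whole 0.25 SD intention-to-treat effect. A negative g of the same size gives a bias of the same size downward.

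**4. Clustering.** Suppose the 80 center mothers come from two neighborhoods, 40 each. The design effect is 1 + 39 × 0.02 = 1.78. For 80 controls over 28 neighborhoods it is 1 + (80/28 − 1) × 0.02 = 1.04. Then SE = √((1.78 + 1.04)/80) = 0.188. A test that allows for this rejects a true null about 19% of the time at g = 0.4 and 36% at g = 0.6, instead of 24% and 48%. The bias itself is unchanged.

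**5. Power under each sampling rule (80 versus 80, clustering ignored).**
- Compliers only: 0.89 for 0.5 SD, but this describes a program effect only if g = 0.
- All assigned mothers: 0.35 for 0.25 SD. About 252 per arm would be needed for power 0.80, and 337 for 0.90.

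**The case against.** The strongest reply is that this is a trade between bias and precision. With random sampling at the same 240 assessments, an instrumental-variable estimate of the complier effect has SE of about 0.158/0.5 = 0.316. The sampling as written has root-mean-square error √(0.158² + bias²) for the same quantity: √(0.025 + 0.04) = 0.255 at g = 0.4, which is smaller, and √(0.025 + 0.09) = 0.339 at g = 0.6, which is larger. The two cross near g = 0.55. This stands, and it is why keeping compliers is a defensible choice. It does not justify reading the contrast as randomized: g is unknown, so the reader cannot tell which side of the crossing applies, and the usual standard error contains no allowance for the bias.

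A second reply is that baseline data allow adjustment and that such detail belongs in an analysis plan. Adjustment is possible, but the sampling rule is fixed in the article itself, and it determines which estimates the data can support. Adjustment would also rest on the untestable assumption that baseline variables capture what separates compliers from the rest.

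Four stronger readings are tempting, and the article does not support them:
- *The effect will be overstated.* Upward bias is plausible, but no gap is given. Families with greater difficulties might also be the ones who stay.
- *The trial's main result is compromised.* PRIDI is the primary outcome, on a random draw of 3000 analyzed by intention-to-treat. Child survival comes from vital registration. Neither uses this sample.
- *This is the only domain-specific developmental result.* The article gives the BSID-III that purpose but does not say PRIDI yields no domain results.
- *The center arm cannot supply 80 compliers.* Two neighborhoods of 120 households at 50% compliance give 120. A shortfall appears only if the sample must come from those endline households and be assessed near age 2 within the six months, and the article fixes neither for the BSID-III. It also reports eight further center neighborhoods from July 2019.

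**Conclusion.** The point holds for the BSID-III/OMCI component and goes no further. Followed as written, the rule produces contrasts of selected compliers with unselected controls, biased by half of g at 50% compliance. Over an assumed g of 0.1 to 0.6 SD, the bias is 0.05 to 0.30 SD and the chance of rejecting a true null is about 6% to 48%. The higher figures fall somewhat when the test allows for clustering. The loss of randomized comparability follows from the text alone. The size depends on g, which the article does not give, and the direction is probably but not certainly upward. Because BSID-III and OMCI are neither the primary nor the named secondary outcome, this limits what the sub-study may claim and does not affect the trial's main conclusion.

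**What to change.** Amend the BSID-III paragraph in the sample-size section to one of two forms.

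**Option A, keep the randomized contrast.** Draw the 80 per arm at random from all mothers assigned to that arm, regardless of compliance, and analyze by assignment. If more compliers are wanted, oversample them but retain non-compliers at known sampling fractions and weight back. A complier effect can then be estimated with assignment as the instrument. State that power for 0.25 SD is only about 0.35 at 80 versus 80 before clustering. The cost is precision, not fieldwork: the same 240 assessments and a new sampling list, feasible before the planned July 2020 start.

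**Option B, keep the compliers.** Model the probability of complying from baseline variables among mothers assigned to each intervention, using the attendance records. Weight the control mothers by their predicted probability. Table 1 already lists suitable baseline data: WAIS, EPDS, parental knowledge and socioeconomic characteristics. Report the result as a non-randomized comparison of compliers, not as a treatment effect by arm, and state the assumption it rests on. No extra data are needed. The costs are some loss of effective sample size among weighted controls and a weaker claim. If the assessments have already been made under the present rule, only this option remains.
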